## Abstract

**Background:**

The number of children and adolescents living with life-limiting conditions and potentially in need for specialised paediatric palliative care (SPPC) is rising. Ideally, a specialised multiprofessional team responds to the complex healthcare needs of children and their families. The questions of, how SPPC is beneficial, for whom, and under what circumstances, remain largely unanswered in the current literature. This study’s overall target is to evaluate the effectiveness of a SPPC programme in Switzerland with respect to its potential to improve patient-, family-, health professional-, and healthcare-related outcomes.

**Methods:**

This comparative effectiveness study applies a quasi-experimental design exploring the effectiveness of SPPC as a complex intervention at one treatment site in comparison with routine care provided in a generalised PPC environment at three comparison sites. As the key goal of palliative care, quality of life - assessed at the level of the patient-, the family- and the healthcare professional - will be the main outcome of this comparative effectiveness research. Other clinical, service, and economic outcomes will include patient symptom severity and distress, parental grief processes, healthcare resource utilisation and costs, direct and indirect health-related expenditure, place of death, and introduction of SPPC. Data will be mainly collected through questionnaire surveys and chart analysis.

**Discussion:**

The need for SPPC has been demonstrated through numerous epidemiological and observational studies. However, in a healthcare environment focused on curative treatment and struggling with limited resources, the lack of evidence contributes to a lack of acceptance and financing of SPPC which is a major barrier against its sustainability. This study will contribute to current knowledge by reporting individual and child level outcomes at the family level and by collecting detailed contextual information on healthcare provision. We hope that the results of this study can help guiding the expansion and sustainability of SPPC and improve the quality of care for children with life-limiting conditions and their families internationally.

**Trial registration:**

Registered prospectively on ClinicalTrials.gov on January 22, 2020. NCT04236180

**Protocol version:**

Amendment 2, March 01, 2021.

## Background

Following ongoing medical advances and improved diagnosis and coding, the number of children and adolescents living with life-limiting conditions is rising drastically [1]. Estimates from the United Kingdom showed a prevalence of 26.7 per 10,000 children aged 0–19 years in 2000/2001, and a prevalence of 66.4 per 10,000 in 2017/2018 [1]. Many of these children and adolescents need palliative care (PC) services. A new consensus describes PC as “the active holistic care of individuals across all ages with serious health related suffering because of severe illness and especially of those near the end of life. It aims to improve the quality of life of patients, their families, and their caregivers.” ([2], p. 761). As a special and highly complex subfield of PC, paediatric PC (PPC) is concerned with the support and involvement of the entire family, and aims to impact the patient-, family and health system levels. Ideally, to meet the complex healthcare needs of children and their families, a specialised multiprofessional team will be available, i.e. PPC services are offered by healthcare professionals specifically trained and working in PPC in the context of a dedicated programme setting [3].

Specialised PPC (SPPC) programmes most commonly offer a consultative model of care, i.e. by a specialised multiprofessional PPC team that either provides direct patient care and family support that goes beyond the affected child’s eventual death or provides support and advice to the child’s primary care team in and outside of the hospital [4]. In such a setup, medical specialists (mainly physicians), e.g. neurologists or oncologists refer their patients and families in need. Referrals are mainly driven by symptom burden and the burden of the child’s condition on the entire family. However, the referral practices also depend on personal attitudes and motivation of the referrers from the medical specialties towards SPPC. Furthermore, the referrer’s perception of evidence supporting SPPC can be considered as a contextual factor influencing referral practices [5] and it is well recognised that compelling scientific evidence on the effectiveness of SPPC is scarce [6–8].

### State of research

The question of whether PC in general is associated with improved patient and caregiver outcomes has been studied and summarised in a meta-analysis of 43 randomised controlled trials with data on 12′731 adult patients [9]. PC interventions were associated with improvements in patient quality of life (QOL) and symptom burden, however, results regarding caregiver outcomes were inconsistent [9]. In PPC, patient-reported outcome assessments are not normally feasible due to the patient’s age or cognitive state. Therefore, in paediatric research, proxy reports from parents are commonly used [10]. A systematic review including eight observational studies found improved QoL in children and family members, improved symptom control, and a positive impact on place of care and family support [11]. The burdens on family members are substantial. Investigating the impact of chronic health conditions on siblings psychological functioning and well-being, Vermaes et al. noted, that the siblings of children with life-threatening conditions appeared especially prone to psychological problems [12]. A recent scoping review, including 34 studies concluded that the experiences these siblings make, impact the way they cope with stress [13]. We found no studies about the influence of SPPC services on the QOL of these siblings.

For healthcare professionals (HCPs), providing compassionate care for children with life-limiting conditions and their families is emotionally demanding. High expectations, lack of support and a sense of inadequate preparation, representing demands from the health care system, can lead to stress in care personnel [14]. One purpose of a consultative SPPC service model is to provide support and advice to each child’s/family’s primary care team, which might ease the care burden and positively influence the QOL of healthcare professionals not specialised in PPC. In a US study of 314 diverse HCPs, 39% were gaged at risk for compassion fatigue (CF), a construct within professional QOL linked to impaired quality of care provision [14, 15].

More evidence related to improved process outcomes at the service level and healthcare resource utilisation is available regarding children/families receiving SPPC. A recent systematic review including 14 cohort studies and one case series found, that the receipt of PPC was associated with a decrease in intensive care use and high-intensity end-of-life care. Regarding hospital admissions, length of stay in hospital, resuscitation orders, and the proportion of hospital and home deaths results were less conclusive [16]. Evidence on healthcare resource utilisation and costs among children, who had accessed a PPC programme versus those, who had not, was summarised in a systematic review [17]. Children enrolled in PPC had fewer hospital admissions, with most studies also showing shorter hospital stays. Conflicting results arose regarding the proportion of patients who received critical care, and calculations of overall healthcare costs were inconclusive [17]. Lower medical costs among PPC recipients through the reduction of healthcare utilisation, however, were recorded in more recent studies [18, 19].

The effectiveness of SPPC as a complex intervention is potentially influenced by many accompanying factors through mechanisms which are not well understood. Important potential mediators of the receipt of SPPC, e.g., the family’s adaptability, should be considered. Based on McCubbin & McCubbin’s resilience model of family stress, adjustment and adaptation, a positive relationship has been described between the family’s adaptation and the family system, i.e., coherence and family hardiness [20]. Associated with adaptation and considered as central to successful coping with family stressors is the construct of sense of coherence. This refers to an orientation between family members, that makes their reactions to internal and external stimuli structured and predictable, providing resistance resources for handling stimuli, and fostering a sense that life’s challenges are meaningful [21]. Family hardiness has been described as a family resource and acknowledged as a mediator in the relationship between stress and illness. As such it has also been related to family members’ health and QOL [22].

### Rationale

As more and more countries have recognised the need for SPPC at the policy level, the international development and implementation of PPC programmes have skyrocketed. However, many of those programmes struggle with the transition into routine in- and outside hospital care and therefore sustainability [4]. The question, of how SPPC is beneficial for whom and under what circumstances, remains largely unanswered as validation of innovative care programmes in controlled studies is lacking [18]. Determining clinical effectiveness will require prospective studies using comparison groups to establish the relationship between the receipt of SPPC and selected outcomes on the client and service levels [23]. Additionally, the question of when to initiate SPPC, and the outcomes of early vs. late introduction of SPPC have never been compared, a comparison of the two has been judged a priority in PPC research [24]. Reporting on outcome metrics at the family level and addressing contextual information on healthcare provision has the potential to guide the expansion and sustainability of services and improve the quality of care for children with life-limiting conditions and their families internationally.

### Objectives

The SPhAERA study’s overall target is to evaluate the effectiveness of SPPC and to report on its potential to improve patient-, family-, health professional-, and healthcare-related outcomes. Specifically,to explore how SPPC influences the QOL of patients (including their symptom severity and distress), parents and siblings (including grief processes);to explore how the availability of an SPPC team influences the QOL of healthcare professionals not specialised in PPC;to determine whether the provision of SPPC reduces the utilisation of healthcare resources and costs;to determine whether the provision of SPPC reduces direct and indirect health-related costs for families; andto evaluate the introduction of SPPC and validation of the Paediatric Palliative Screening Scale (PaPaS-Scale) [25].

## Methods

### Design and setting

This study applies a quasi-experimental design within the framework of comparative effectiveness research, exploring the effectiveness of SPPC as a complex intervention in comparison with routine care provided in a non-specialised PPC environment. The study takes place at four study sites: the largest Swiss University Children’s Hospital with a longstanding established dedicated SPPC programme serves as the intervention site, two other Swiss university children’s hospitals and a Cantonal children’s hospital providing general PPC and are just developing SPPC comprise the comparison sites. Recruitment took place between November 2019 and May 2022, and the longitudinal data collection is ongoing until May 2023. An overview of the study’s setup, timeline and outcomes is provided in Fig. 1.

**Fig. 1 Fig1:**
[figure not shown]
Overview of the study’s setup, timeline and outcomes

### Participants and recruitment

#### Patients and families

Children suffering from a life-limiting condition and potentially in need of SPPC, their parents and siblings, as applicable, were eligible to enter the study under the following inclusion criteria: 1) children, aged 0–18 years; parents (mothers and/or fathers) of included children; 2) siblings, aged 8–18 years, of included families; 3) proficiency in German or French language. Neonates with medical complications due to prematurity and/or birth complications and treated in a neonatal intensive care unit and patients enrolled in the SPPC programme with an expected life expectancy of < 48 h were excluded due to limited exposure time. Additionally, children and their families under child protection regulations were not eligible.

For the intervention site, all children entering the SPPC programme, after referral by a member of the frontline care team (usually a physician), were prospectively and consecutively screened for eligibility and invited for study participation. Recruitment was then performed by a member of the SPPC team within the first 2 weeks of SPPC initiation.

For the comparison sites, recruitment started in February 2020 and was performed by specialists of various medical disciplines, e.g. neurology or oncology after evaluating the potential need for SPPC of their patients. This need was defined per indication criteria of the SPPC programme at the intervention site and read as follows: 1) increase in (unplanned) hospital admissions during the last months; 2) adverse medical events from which the child is not recovering completely; 3) increasing symptom burden; unsatisfactory response to treatments; 4) conflicting treatment goals; 5) estimated life expectancy less than 6–12 months; 6) patient’s/parents’ wish for PC support [26].

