#### Primary and secondary analyses

The primary outcome QOLLTI-F of the care-giving parents 1 month after study inclusion will be analysed by a linear mixed-effects model with QOLLTI-F at baseline and group (SPPC vs. comparison) as fixed effects. A random intercept will be modelled per patient (to account for the non-independence of parents from the same patient). In addition, all measurements of QOLLTI-F taken at different follow-up visits will be analysed by a linear mixed-effects model as above, but with an additional random intercept per parent (to additionally account for the non-independence of multiple measurements per parent).

To adjust the effect size estimate for SPPC vs. comparison for potential confounders, we will use propensity score weighting. Potential confounders were already identified and include characteristics of the patient (diagnosis, age, sex), disease duration, family system (sense of coherence, family hardiness), sociodemographic variables of the family (e.g. parental living situation, family income), and contextual information (e.g. study site characteristics). As a sensitivity analysis, we will add the most important confounders as covariates in the statistical models (analysis of covariance approach).

Secondary endpoints will be analysed by linear mixed-effects models or generalised linear mixed-effects models (in case of non-normal error distribution). Normal linear models or generalised linear models may be used for secondary outcomes measured only once per patient. Sensitivity analyses will be performed as applicable and appropriate.

Missing measurements of the primary outcome, QOLLTI-F at 1 month, will be multiply imputed, based on measurements taken at 2 weeks (first follow-up measurement) and available patient characteristics.

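### In the SPPC group the baseline QOLLTI-F may be taken 0 to 14 days after SPPC began, yet the primary model adjusts for it; the under-48-hour exclusion is worded for that group only.

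*Protocol article*

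**What the plan says.** The protocol article (Participants and recruitment, Patients and families) starts the two groups differently. In the SPPC group, "all children entering the SPPC programme, after referral by a member of the frontline care team (usually a physician), were prospectively and consecutively screened", and then: "Recruitment was then performed by a member of the SPPC team within the first 2 weeks of SPPC initiation". At the comparison sites recruitment "was performed by specialists of various medical disciplines, e.g. neurology or oncology after evaluating the potential need for SPPC of their patients". No index event or time window is given there.

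Intervention and comparison counts everything that the SPPC team provides to a family as study intervention, so exposure begins at SPPC initiation. Table 1 places the first QOLLTI-F at study entry. Primary and secondary analyses sets the primary endpoint one month after inclusion, not after SPPC start, and fits a mixed model "with QOLLTI-F at baseline and group (SPPC vs. comparison) as fixed effects". The propensity score includes sense of coherence and family hardiness, which Table 1 also schedules at enrolment.

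On early death, the same recruitment section says "patients enrolled in the SPPC programme with an expected life expectancy of < 48 h were excluded due to limited exposure time". The need criteria used at the comparison sites include "estimated life expectancy less than 6–12 months" and state no lower limit.

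**The concern.** A baseline covariate should precede treatment. Here it precedes treatment at the comparison sites, where no SPPC programme entry occurs, but may follow it by up to two weeks at the intervention site. If SPPC has already raised parental QOL by then, the group difference at baseline contains some of the treatment effect. Conditioning on baseline then removes part of what the trial wants to estimate. Sense of coherence and family hardiness share the timing. Table 1 lists them as mediators, so weighting on values taken after SPPC began could remove a further part.

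The exclusion is a separate eligibility mismatch. Read literally, a child judged to be within two days of death is ineligible in one group and eligible in the other. Place of death, intensive care admissions and resuscitations are study outcomes, so the two groups' analysis sets should follow the same rule.

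**Working it through.** **The plan's own figure.** Inputs from Sample size and statistical analyses: difference 1 point, SD 1.7, correlation between parents 0.8, one parent only for 30% of patients, power 0.80, alpha 0.05 (two-sided assumed), drop-out 10%.

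- Variance of a two-parent mean: 1.7² × (1 + 0.8)/2 = 2.601. Variance for one parent: 1.7² = 2.89.
- Combined per patient: 1/(0.7/2.601 + 0.3/2.89) = 2.681.
- The normal approximation gives 43 per group, 86 in total, and 86/0.9 = 96. The noncentral t gives 88 evaluable (power 0.808), and 88/0.9 = 98.

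The stated 98 is reproduced. The problem is what the adjusted model estimates, not the sample size arithmetic.

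**Size of the possible bias.** Let D1 be the true group difference at one month, f the share of it already present at baseline because of SPPC, and r the slope of the one-month score on baseline. The expected baseline-adjusted difference is D1 − r × f × D1 = D1 × (1 − r × f).

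The article gives neither f nor r, so both are assumed. With linear build-up from SPPC start and the endpoint 30 days after inclusion, f = delay/(delay + 30).

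| Delay | f | Estimate of a true 1-point effect, r = 0.5 | r = 0.7 |
|---|---|---|---|
| 0 days | 0 | 1.00 | 1.00 |
| 7 days | 7/37 = 0.19 | 0.91 | 0.87 |
| 14 days | 14/44 = 0.32 | 0.84 | 0.78 |

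Table 2 allows one week to complete a form. That could lengthen the delay and is not counted here.

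**Power with 88 evaluable patients at f = 0.32.**

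- Sample size variance kept at 2.681: power falls from 0.81 to 0.66 (r = 0.5) or 0.59 (r = 0.7).
- Precision gain from baseline adjustment credited (variance × (1 − r²), which treats r as a correlation): 0.78 against 0.905 with a clean baseline at r = 0.5, and 0.87 against 0.98 at r = 0.7.

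Neither set allows for the loss of precision from propensity weighting.

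**The exclusion.** The lower limit of 48 hours is attached to enrolment in the SPPC programme, and the comparison criteria set only an upper bound. No other section extends the limit to the comparison group. A comparison child who dies very early could count as a drop-out (if no QOLLTI-F was obtained) or receive an imputed one-month value, while the SPPC counterpart would never have entered. For resuscitation and place of death, keeping such children could make the comparison group look worse. For cumulative stay and cost, a child who lives under two days adds little, which lowers that group's totals.

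**The case against.** The recruitment window permits entry on day 0, and the actual delays are not reported. A reader might infer that every SPPC baseline is post-treatment; the text supports only a delay of 0 to 14 days. Nor does the article say that parental QOL moves within days of first contact. With no early effect there is no bias, and if first contact lowered scores the sign would reverse. A reader might also suppose that half the effect could already be in the baseline. Under linear build-up even a 14-day delay gives only 32%. With the adjustment gain credited, power stays near or above the planned 0.80. All of this stands, and it limits the size of the point without removing it.

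On the exclusion, the stated reason is limited exposure, nothing shows that comparison sites enrolled imminently dying children, and few such families are likely. A reader might infer that the asymmetry favours SPPC on cost. The article does not support that, because very early death shortens the period over which cost accrues.

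The earlier recruitment start at the intervention site (November 2019, against February 2020 at the comparison sites) is also tempting to cite, but nothing in the article shows how it would bias the comparison.

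The Discussion concedes a risk of confounding and relies on propensity scoring and multilevel modelling. Neither restores a pre-treatment baseline. Nor is this detail merely left to an analysis plan: the window, the exclusion and the primary model are all stated, and together they create the problem.

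**Conclusion.** The point holds in limited form. The primary model conditions on a QOLLTI-F score that, in the SPPC group only, may follow treatment start by 0 to 14 days. If early contact improves parental QOL, the adjusted effect is biased toward zero. Under linear build-up, delays of 7 to 14 days and slopes of 0.5 to 0.7, a true 1-point effect would be estimated as about 0.78 to 0.91. With entry on day 0 it would be unbiased on this account. These are assumed ranges, and the true size is unknown until the delays are reported. The 98-patient target is not in question.

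The eligibility wording differs between groups. The effect is probably small and differs in direction by outcome. A null or reduced primary result could not be read cleanly without the delay data.

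**What to change.** Recruitment has closed, but data collection runs to May 2023, so the remedy lies in the analysis.

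1. Take the date of first SPPC contact from the chart and report the distribution of days from that date to the baseline QOLLTI-F.
2. Keep baseline adjustment in the primary model. Pre-specify a sensitivity analysis restricted to SPPC families with baseline within a few days of first contact, or one that models the delay. Fix the cut-off before outcomes are examined. An analysis without baseline may be shown only as supportive, labelled as losing confounding control: in a non-randomised comparison it cannot isolate this bias.
3. Reconcile the exclusion wording so that the same rule defines the analysis set in both groups. Use life expectancy documented at entry where available. Otherwise add a sensitivity analysis that removes deaths within 48 hours of entry from both groups alike.
4. State with the primary result that it may understate the effect, and that the enrolment measures used in the propensity score share the timing.

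The cost is one chart date per SPPC family, some analysis-plan wording, and less precision in the restricted analyses. Families enrolled early may also differ from those enrolled late, so the restricted result is a check and does not replace the primary one.
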